#### **4.11. Timing of final analysis**

The final analysis for the trial will occur once all participants have completed the 1-year assessment and the corresponding outcome data has been entered onto the trial database and validated as being ready for analysis. This is provided that the trial has not been stopped early for any reason (e.g. TSC advice or funding body request).

#### **4.12. Timing of other analyses**

Not applicable.

#### **4.13. Trial comparisons**

All references in this document to ‘group’ refer to carvedilol or band ligation.

## 5. Statistical Principles

### 5.1. Confidence intervals and p-values

All estimates of differences between groups will be presented with two-sided 95% confidence intervals, unless otherwise stated. P-values will be reported from two-sided tests at the 5% significance level.

### 5.2. Adjustments for multiplicity

No correction for multiple testing will be made.

### 5.3. Analysis populations

All primary analyses (primary and secondary outcomes including safety outcomes) will be by intention-to-treat (ITT). Participants will be analysed in the intervention group to which they were randomised, and all participants shall be included whether or not they received the allocated intervention. The analysis population for the four week safety form will comprise only those patients randomised to carvedilol. This is to avoid any potential bias in the analysis.

### 5.4. Definition of adherence

Adherence to allocated intervention will be monitored via a participant's medical notes. In particular, in the carvedilol arm, participants will be asked about adherence with their trial medication at each follow-up visit and their response documented in the medical notes and subsequently transcribed onto the Follow-Up CRFs. Adherence to variceal band ligation will be documented on the Follow-Up CRFs using information available in the participant's medical notes.

We will define adherence as follows:

#### Carvedilol Arm

A participant randomised to the carvedilol arm is considered adherent if they report taking their dose of trial medication at least 75% of the time until the end of the trial or until they stop/switch treatment due to medical reasons.

#### Variceal Band Ligation Arm

A participant randomised to variceal band ligation is considered adherent if they attend all scheduled banding appointments. Note that a rescheduled appointment is not considered missed and that varices may not be eradicated if a person stops/switches treatment due to medical reasons.

In the case that withdrawal, death or loss to follow-up lead to early exit from the trial, adherence is based on adherence information collected up the point of exit.

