##### Variceal Band Ligation

The procedure will be performed as per the British Society of Gastroenterology guidelines. Varices are banded at regular intervals (usually two to four weekly) until they are eradicated when they are normally replaced by scar tissue or by varices of much smaller size. Participants usually require on average 2-3 banding procedures to achieve eradication. After successful eradication of the varices, participants have a repeat endoscopy at approximately three

months, then at approximately six monthly thereafter. Any recurrent varices (i.e. medium to large varices) are treated with further variceal band ligation until eradication and then offered repeat endoscopy at approximately six monthly intervals.

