### **9.10. Sensitivity analyses**

Sensitivity analyses will be limited to the primary outcome and will consist of:

- An analysis is performed the same way as the primary analysis described in section 9.5 but now limited to the population that adhered to the allocated intervention as described in section 5.4.
- An analysis is performed to assess the effect of missing responses, in particular, the risk of bias they present. In the primary analysis described in section 9.5, all those recruited who have not reported variceal bleeding within 12 months are assumed to not have experienced the event. Here it is assumed that those who did not report variceal bleeding but have withdrawn, are lost to follow-up or have died within the 12-month follow-up period are missing the primary outcome response. Note that participants who are still actively in the trial at 12-months (are not withdrawn or lost to follow-up) but do not return the 12-month follow-up form will not be assumed missing.

Making these assumptions, firstly, an analysis is performed restricted to the population which has non-missing responses. Secondly, it is assumed that those with a missing response did not have variceal bleeding - the rationale being that the trial team would be

aware if bleeding had occurred due to the seriousness of the event and subsequent completion of an SAE form. Thirdly, the missing responses are assumed to be missing at random and are imputed via multiple imputation. In these three scenarios, the subsequent analysis performed is conducted in the same fashion as the primary analysis described in section 9.5.

- An analysis is performed on the primary analysis population in the same way as described in section 9.5 but with no covariate adjustment.

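### The SAP's adherence rule does not stop at the first variceal bleed in either arm, so behaviour after the outcome can decide who enters the adherent-population analysis

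*SAP*

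**What the plan says.** Section 5.4 defines adherence separately for each arm.

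- **Carvedilol.** A participant is adherent "if they report taking their dose of trial medication at least 75% of the time", assessed "until the end of the trial or until they stop/switch treatment due to medical reasons".
- **Banding.** A participant is "considered adherent if they attend all scheduled banding appointments". No end to the window is given in that sentence. A note follows: "Note that a rescheduled appointment is not considered missed and that varices may not be eradicated if a person stops/switches treatment due to medical reasons".
- **Early exit.** The section closes with "In the case that withdrawal, death or loss to follow-up lead to early exit from the trial, adherence is based on adherence information collected" as far as that exit. A variceal bleed is not among the listed reasons for closing the window.

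Section 9.10 then plans a sensitivity analysis of the primary outcome, run like the primary analysis but "limited to the population that adhered to the allocated intervention as described in section 5.4". Section 7.2 tabulates the same adherence categories by arm.

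The primary outcome (sections 4.3 and 9.4) is settled by the onset date of the first variceal bleed, if that falls within 365 days of randomisation. Section 5.3 makes the primary analysis intention-to-treat.

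**The concern.** Once a participant has bled within the year, the primary outcome is fixed, and nothing done later can change it. Under section 5.4, later conduct still counts towards adherence. A banding participant who bleeds in month 3 and misses an appointment outright in month 8 is non-adherent and leaves the section 9.10 analysis as a lost event. A carvedilol participant who bleeds in month 3 and then takes fewer doses without a medical reason can be lost in the same way. That is selection on behaviour after the outcome.

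A second problem is that the medical stop/switch provision is uneven. For carvedilol it plainly ends the window. For banding it appears only in a remark on why varices may remain, and whether appointments after the stop still count is not stated. Two statisticians could derive different adherent populations from the same data.

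Section 9.10 contains the only planned analysis of the primary outcome restricted to adherers. If it differs from the intention-to-treat result, or agrees with it, the reader cannot tell how much of that comes from who was removed after bleeding.

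**Working it through.** **The plan's own figure.** Section 4.7 uses 12% versus 8%, two-sided 5%, 90% power and 1:1 allocation. With the pooled-variance formula and mean risk 0.10:

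n = [1.960·√(2·0.10·0.90) + 1.282·√(0.12·0.88 + 0.08·0.92)]² / 0.04², which rounds up to 1181 per group, 2362 in total, as stated. Dividing by 0.9 for attrition gives 2625, close to the stated 2630. The 12% and 8% are therefore used below as the design risks.

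**When each window closes under section 5.4**

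| Event | Carvedilol | Banding |
|---|---|---|
| First variceal bleed | no | no |
| Medical stop or switch | yes | unclear |
| Withdrawn, died or lost | yes | yes |

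**Effect on the risk ratio.** Let p be the true risk in an arm, q0 the share of non-bleeders who are non-adherent and q1 the share of bleeders who are. The risk seen among adherers is

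r = p(1−q1) / [p(1−q1) + (1−p)(1−q0)].

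The SAP gives neither q0 nor q1, so both are assumed. First take the banding arm alone (p = 0.12), with carvedilol non-adherence unrelated to bleeding, so that the carvedilol risk stays at 8% (design effect) or 12% (no effect). With q0 = 10% and q1 = 20%:

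r = 0.12·0.80 / (0.12·0.80 + 0.88·0.90) = 0.096/0.888 = 10.8%.

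RR = 0.08/0.108 = 0.74 (design effect) and 0.12/0.108 = 1.11 (no effect). With 1315 in the arm, the extra bleeders removed number 1315·0.12·0.10 ≈ 16.

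| q0 | q1 | Banding risk among adherers | RR, design effect | RR, no effect |
|---|---|---|---|---|
| 10% | 0% | 13.2% | 0.61 | 0.91 |
| 10% | 10% | 12.0% | 0.67 | 1.00 |
| 10% | 20% | 10.8% | 0.74 | 1.11 |
| 10% | 30% | 9.6% | 0.83 | 1.25 |
| 20% | 10% | 13.3% | 0.60 | 0.90 |
| 20% | 30% | 10.7% | 0.75 | 1.13 |

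**Because the carvedilol window also runs past the bleed**, the same selection can act there. With q0 = 10% and q1 = 20% in carvedilol under the design effect, r = 0.08·0.80 / (0.08·0.80 + 0.92·0.90) = 0.064/0.892 = 7.17%.

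- In carvedilol only: RR = 0.0717/0.12 = 0.60 (design effect) and 0.108/0.12 = 0.90 (no effect).
- In both arms equally: RR = 0.0717/0.108 = 0.66 (design effect) and 1.00 (no effect).

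The shift thus depends on how the selection differs between arms, and the SAP does not determine that.

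**The case against.** The strongest reply is that no rule excludes anyone for bleeding. A banding participant leaves the adherent set only by missing an appointment outright, and a rescheduled one does not count as missed. Section 5.4 also closes the window at death, so some bleeders have fewer appointments to miss. All of this stands, and it limits how large the effect can be.

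Three stronger readings are tempting, but the SAP does not support them.

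- **That banding bleeders are removed because they bled.** A reader might infer this by supposing that a bleed leads to more banding appointments. Section 4.2 ties further banding to recurrent varices, not to bleeding. It says "Participants usually require on average 2-3 banding procedures to achieve eradication" and gives no count for bleeders. Even if one assumes 5 appointments for bleeders against 3 for others, a 2% chance of missing each gives a banding risk of 0.12·0.98² / (0.12·0.98² + 0.88) = 11.6% and RR 0.69, against 0.67.
- **That the problem is confined to banding and must favour it.** The carvedilol window also runs past the bleed. The SAP does not say that stopping carvedilol after a bleed counts as a medical reason. The direction reverses if bleeders adhere better, or if the selection falls mainly on carvedilol.
- **That different thresholds are themselves an error.** Requiring all banding appointments but 75% of doses is a defensible choice for a few procedures against daily tablets. A 75% bar for banding would change nothing for the usual 2 or 3 sessions, since 2 of 3 is 67% and one miss already fails.

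The reply does not meet the point that conduct after the first bleed counts towards inclusion in both arms. Nothing else in the SAP prevents it.

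**Conclusion.** The point holds in limited form. Section 5.4 assesses adherence beyond the first bleed in both arms and is unclear on whether a medical stop or switch ends the banding window. The section 9.10 adherent-population analysis can therefore keep or drop bleeders on behaviour that came after their outcome.

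The size is unknown. A 10-point excess of non-adherence among banding bleeders alone, over 10% in non-bleeders, moves the risk ratio by about 0.07 under the design effect and 0.11 under no effect. A 10-point deficit moves it the other way, and equal selection in both arms nearly cancels. These figures rest on assumed adherence rates and show only what the rule allows.

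The intention-to-treat primary analysis is untouched. What is weakened is the plan's only check of the primary result in adherers.

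**What to change.** In section 5.4, state that for the section 9.10 analysis adherence is derived in both arms only up to the earliest of first variceal bleed, medical stop or switch, early exit, or day 365. Word the stop/switch rule identically for both arms. The thresholds can stay as they are, and the section 7.2 table can keep describing adherence over the whole period if labelled so. This concerns the derivation of an analysis population only, not how participants are treated.

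**Cost.** SAP wording and a re-derived flag. The first-bleed date is already needed for the primary outcome. Banding appointment dates would have to be taken from the medical notes that section 5.4 already uses. Carvedilol adherence is self-reported, and Appendix C schedules its collection only at 6 and 12 months, so its cut at the bleed date will be approximate.

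**What remains.** The cut restores 12% in banding, and so 0.67 and 1.00, only if bleeders and non-bleeders are equally often non-adherent within their assessed windows. Bleeders' windows will be shorter, and an all-appointments rule is easier to meet over fewer appointments. For example, assume 95% attendance per appointment, with 2 appointments for bleeders and 3 for others. Then r = 0.12 / (0.12 + 0.88·0.95) = 12.6% and RR = 0.64. The analysis should therefore still be read as supportive, but it would no longer depend on conduct after the outcome.

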## **5.5. Handling protocol deviations and violations**

A protocol deviation/violation is defined as a failure to adhere to the protocol such as errors in applying the inclusion/exclusion criteria, the incorrect intervention being given, incorrect data being collected or measured, follow-up visits outside the visit window or missed follow-up visits. We will apply a strict definition of the ITT principle and will include all participants as per the ITT population described in section 5.3 in the analysis in some form regardless of deviation from the protocol. This includes participants who were randomised but later found to violate the inclusion or exclusion criteria. This does not include those participants who have specifically withdrawn consent for the use of their data in the first instance; however these outcomes will be explored as per other missing responses.

## **5.6. Unblinding**

This is an open label study and the allocated intervention is recorded on the case report forms. Interim analyses will be produced by trial arm (i.e. Carvedilol vs. variceal band ligation) Unblinding of the Trial Statistician to the allocated intervention code will take place prior to each of the interim analyses (with enough time to produce the report) and after the database is locked for final analysis.

# **6. Trial population**

## **6.1. Recruitment**

A flow diagram (as recommended by CONSORT) will be produced to describe the participant flow through each stage of the trial. This will include information on the number (with reasons) of losses to follow-up (drop-outs and withdrawals) over the course of the trial. A template for reporting this is given in the final report template.

## **6.2. Baseline characteristics**

The trial population will be tabulated as per the table in the final report template. Categorical data will be summarised by number of participants, counts and percentages. Continuous data will be summarised by the number of participants, mean and standard deviation if deemed to be normally distributed or number of participants, median and interquartile range if data appear skewed, and ranges if appropriate. Tests of statistical significance will not be undertaken, nor confidence intervals presented.

# **7. Intervention(s)**

## **7.1. Description of the intervention(s)**

A template for reporting information on the intervention(s) is given in the final report template. As variceal band ligation is a surgical intervention this includes information such as the number of banding procedures needed to eradicate the varices.

## **7.2. Adherence to allocated intervention**

A cross-tabulation of allocated intervention by the adherence categories stated in section 5.4 will be produced (proportions and percentages). A template for reporting adherence is given in the final report template. This includes tables for reporting information such as whether the additional 4-week follow-up visit was attended by those in the carvedilol group.

## **8. Protocol deviations and violations**

Frequencies and percentages by group will be tabulated for the protocol deviations and violations as per the final report template.

## **9. Analysis methods**

### **9.1. Covariate adjustment**

In the first instance, intervention effects between groups for all outcomes will be adjusted for the minimisation parameters listed in section 4.6. Categorised continuous variables (e.g. age) will be treated as continuous variables in this adjustment. Other covariate adjustment will be baseline values for parameters where available (e.g. EQ-5D-5L will be adjusted for baseline score).

If covariate adjustment is not possible (e.g. the model does not converge), unadjusted estimates will be produced, and it will be made clear in the final report why this occurred (e.g. not possible due to low event rate/lack of model convergence).

If the log-binomial model fails to converge, a Poisson regression model with robust standard errors will be used to estimate the same parameters. If this also fails to converge, unadjusted estimates will be produced from the log-binomial model. It will be made clear in the final report why this occurred (e.g. not possible due to low event rate/lack of model convergence).

### **9.2. Distributional assumptions and outlying responses**

Distributional assumptions (e.g. normality of regression residuals for continuous outcomes) will be assessed visually prior to analysis; although in the first instance the proposed primary method of estimation in this analysis plan will be followed. If responses are considered to be particularly skewed and/or distributional assumptions violated, the impact of this will be examined through sensitivity analysis; this will consist of transformation of responses prior to analysis (e.g. log transformation) in the first instance. If extreme values are apparent and considered to be affecting the integrity of the analysis, a sensitivity analysis consisting of removing the outlying response(s) and repeating the analysis will be performed. Output from these analyses, if performed, will be described and presented alongside the original analysis (or included, e.g. in appendices) with the excluded values clearly labelled. See section 9.10 for further details.

### 9.3. Handling missing data

In the first instance, analysis will be completed on received data only with every effort made to follow-up participants even after protocol violation to minimise any potential for bias. For the primary outcome, a participant will be assumed to not have experienced variceal bleeding unless there is evidence to suggest otherwise. Therefore, there will be no missing data in this outcome for the primary analysis. However, sensitivity analysis will be performed on the primary outcome measure. See section 9.10 for further details.

### 9.4. Data manipulations

The Trial Statistician will derive all responses from the raw data recorded in the database.

#### **Primary outcome measure**

The primary outcome measure for the comparison of carvedilol vs. variceal band ligation is variceal bleeding within 1 year of randomisation. We will define 1 year to be 365 days.

Variceal bleeding events are identified on the 6 month and 12 month follow-up forms. If a participant has at least one episode of variceal bleeding (including banding-related bleeding) indicated on either of these follow-up forms then they have “experienced variceal bleeding”. Participants which do not fulfil this criteria for experiencing variceal bleeding will be termed “free from variceal bleeding”.

For the primary outcome analysis, if a participant has “experienced variceal bleeding” and the date of onset of the first episode of bleeding as indicated on the follow-up form is within 365 days of the date of randomisation then the question “Has variceal bleeding occurred within 1 year of randomisation?” will be answered “yes”. Otherwise, it will be answered “no”. This will form the primary binary outcome.

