#### **Secondary outcome measures**

##### *Time to first variceal bleed*

Variceal bleeding events are identified as adverse events on the 6 month and 12 month follow-up forms. If a participant has at least one episode of variceal bleeding (including banding-related bleeding) indicated on either of these follow-up forms then they have “experienced variceal bleeding”. Participants which do not fulfil this criteria for experiencing variceal bleeding will be termed “free from variceal bleeding”.

If a participant is termed as having “experienced variceal bleeding” then their time until bleeding will be defined as the number of days from the date of randomisation till the date of onset for the first variceal bleed occurring.

Participants who are termed as “free from variceal bleeding” and who were last known to be

bleeding-free prior to the 12-month follow-up time-point will be censored in the analysis. The time to censoring will be the number of days from the date of randomisation to the date last known to be free from variceal bleeding. This will be determined by the completion date of the most recent trial form received e.g. date of completion on the 12-month follow-up form. If the last known date in the trial is equal to the date of randomisation then the participant will be censored at day 1.

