#### All-cause mortality at one year

Deaths are identified on the SAE form. If a participant has death indicated on an SAE form via the 'death' variable then they will be termed "dead". Participants which do not fulfil this criteria will be termed "alive".

If a participant is "dead" then their time till death will be defined as the number of days from the date of randomisation till the date death. If the time till death is  $\leq 365$  days then the question "All-cause mortality occurred by one year?" is termed "yes". If the time till death is  $> 365$  days then the question "All-cause mortality occurred by one year?" is termed "no".

If a participant is "alive" then their time till censoring will be the number of days from the date of randomisation to the date last known to be alive. This will be determined by the completion date of the most recent trial form received. If the censored time is  $> 365$  then the question "All-cause mortality occurred by one year?" is answered "no". If the censored time  $\leq 365$  days but the follow-up CRF has been completed within the window of assessment (no earlier than 351 days from randomisation) then "All-cause mortality occurred by one year?" is answered "no". If the censored time is  $\leq 365$  and the 12-month follow-up CRF has not been returned within the scheduled window of assessment then there is not complete information regarding mortality within 1 year for this participant. Therefore, the answer to "All-cause mortality occurred by one year?" is considered to be missing.

Liver-related mortality and cardiovascular mortality will be derived in a similar fashion. Deaths of these types will be classified and indicated on the database following review of the SAE information provided by the chief investigator.

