## Appendix C: Schedule of assessments

**Table of Assessments**

|                                                     | Randomisation
and Baseline | 4 weeks ‡ ± 1
week
FU visit | 6 months ± 2
months FU visit | 12 months ± 2
months FU visit |
|-----------------------------------------------------|-------------------------------|----------------------------------------------|---------------------------------|----------------------------------|
| Confirm eligibility                                 | ✓                             |                                              |                                 |                                  |
| Seek informed consent                               | ✓                             |                                              |                                 |                                  |
| Randomisation                                       | ✓                             |                                              |                                 |                                  |
| Medical history #                        | ✓                             |                                              |                                 |                                  |
| Medication review                                   | ✓                             | ✓                                            | ✓                               | ✓                                |
| Physical examination                                | ✓*                            |                                              | ✓*                              | ✓*                               |
| Office blood pressure                               | ✓                             | ✓                                            | ✓                               | ✓                                |
| Pulse                                               | ✓                             | ✓                                            | ✓                               | ✓                                |
| Standard care blood tests                           | ✓*                            |                                              | ✓*                              | ✓*                               |

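### The primary outcome is coded as no bleed through day 365 even when the 12-month form was completed earlier, and the SAP gives two conflicting windows for that form

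*SAP*

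**What the plan says.** Section 9.4 (Primary outcome measure) fixes the period: "We will define 1 year to be 365 days". It then names the source of events: "Variceal bleeding events are identified on the 6 month and 12 month follow-up forms". A participant with a bleed on either form, with onset within 365 days of randomisation, is a yes, and everyone else is a no. The completion date of the form plays no part.

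Section 9.3 supports this with a default: "a participant will be assumed to not have experienced variceal bleeding unless there is evidence to suggest otherwise". It concludes: "Therefore, there will be no missing data in this outcome for the primary analysis".

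On when the 12-month form may be completed, the SAP gives two answers:

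- Appendix C heads the column "12 months ± 2 months FU visit", and the EQ-5D-5L paragraph of 9.4 also gives ± 2 months as the scheduled window of assessment.
- The mortality paragraph of 9.4 accepts a form at or before day 365 only if it falls within a window described as "no earlier than 351 days from randomisation". The transplant-free survival paragraph repeats that limit.

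For time to first bleed, a bleed-free participant is censored at the date last known to be free of bleeding: "This will be determined by the completion date of the most recent trial form received e.g. date of completion on the 12-month follow-up form".

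In section 9.10, the primary outcome counts as missing only for participants without a reported bleed who withdrew, were lost to follow-up or died within the 12 months.

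**The concern.** A participant may attend within the window in Appendix C, have a complete 12-month form, and still have up to two months of the primary outcome period ahead of them. A first bleed in that time is on neither follow-up form, so the derivation returns no bleed. The participant has not withdrawn, been lost or died, so neither the complete-case analysis nor the multiple imputation in 9.10 touches them.

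The reported one-year risk would then be, for some participants, the risk over a shorter period. Absolute risks and the risk difference would be too small and some power would be lost. The stated absence of missing data would hold by assumption and not by observation. The risk ratio would be affected only if early forms were more common in one arm, and the SAP has no check for that.

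**Working it through.** **One participant under three rules.** Take a living, bleed-free participant whose last form is the 12-month form, completed on day 310.

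| SAP 9.4 derivation | Treatment of this participant |
|---|---|
| Time to first bleed | Censored at day 310 |
| All-cause mortality | One-year status missing (form before day 351) |
| Primary outcome | No bleed through day 365 |

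Two secondary outcomes recognise the incomplete observation. The primary outcome does not.

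**Reproducing the plan's figure.** The inputs from section 4.7 are 12% against 8%, two-sided 5%, 90% power and 1:1 allocation. With pooled variance and no continuity correction,

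n = [1.960 √(2 × 0.10 × 0.90) + 1.282 √(0.12 × 0.88 + 0.08 × 0.92)]² / 0.04²,

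which rounds up to 1181 per arm, 2362 in total, as stated. Dividing 2362 by 0.9 gives 2625, against the stated 2630 (1315 per group), close enough to be rounding.

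**Length of the gap.** Two months is 365/6 = 60.8 days, so month 10 is day 304. The gap is at most 365 − 304 = 61 days (61/365 = 16.7% of the period). Under the day-351 window it is at most 365 − 351 = 14 days.

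**Effect on the observed risks.** The SAP does not give the timing of bleeds within the year, so a constant hazard is assumed here. The risk observed by day d is then 1 − (1 − p)^(d/365). For d = 304:

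- Banding: 1 − 0.88^(304/365) = 10.1%, so 1315 × (0.1200 − 0.1010) ≈ 25 bleeds missed per 1315.
- Carvedilol: 1 − 0.92^(304/365) = 6.7%, so 1315 × (0.0800 − 0.0671) ≈ 17 bleeds missed per 1315.

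| Timing of 12-month forms, same in both arms | Observed risks | Risk ratio | Bleeds missed per 1315 | Power at 1181 per arm |
|---|---|---|---|---|
| All at day 365 or later | 12.0% / 8.0% | 0.667 | 0 / 0 | 90.0% |
| All at day 351 | 11.6% / 7.7% | 0.666 | 6 / 4 | 88.9% |
| Spread evenly over days 304–426 (mean gap 15 days) | 11.5% / 7.7% | 0.666 | 6 / 4 | 88.8% |
| All at day 304 (worst case) | 10.1% / 6.7% | 0.664 | 25 / 17 | 84.4% |

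In the worst case the risk difference falls from 4.0 to 3.4 points. At the full 1315 per arm, power in that case is 88.0%.

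**Sensitivity to the hazard.** If the hazard in the last two months is half the earlier rate, the worst-case risks are 11.0% and 7.3%. Front-loaded bleeding therefore makes the loss smaller.

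**The case against.** The strongest reply is that these bleeds are not lost to the trial. Section 9.10 argues that the team would learn of a bleed through an SAE form, and the default in 9.3 yields to contrary evidence. A reader might infer from the window alone that up to 61 days are never observed; the SAP does not support that. What stands is narrower. The derivation in 9.4 does not name the SAE form as a source of bleeds, although the death and transplant derivations do name it, so a bleed reported only on an SAE form is still coded no.

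Second, the ± 2 months in Appendix C belongs to the visit, and nothing says the form closes on that day. Section 5.4 shows that Follow-Up CRFs draw on the medical notes. Where 9.4 speaks of completing the CRF it gives day 351, which would limit the gap to 14 days. That reading is fair, but the EQ-5D-5L paragraph calls ± 2 months the scheduled window, so the document does not settle it. Day 351 also cannot be read as a check meant for mortality alone, since transplant-free survival uses it too. The protocol's visit schedule and any CRF guidance, which might resolve this, were not at hand.

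Third, the time-to-bleed analysis already censors at form completion. It does so only as a secondary outcome and leaves the primary derivation unchanged.

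Two further inferences are tempting and not supported. One is that the open-label design biases the risk ratio. Appendix C gives both arms the same 6- and 12-month visits, and nothing ties the 12-month form to the banding endoscopies. The other is that cost per bleed avoided would be too low. Bleeds avoided is the denominator, so a smaller risk difference would raise that ratio, other things equal.

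**Conclusion.** The point holds as a gap in the primary derivation together with an unreconciled window. A first bleed after an early 12-month form and before day 365 is coded as no bleed, and no planned sensitivity analysis of the primary outcome addresses it.

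The effect is probably modest. It is about half a percentage point or less on each arm's risk and about one point of power if visits are spread evenly over the window. At worst it is about 1.9 and 1.3 percentage points on the two risks and about 6 points of power. These figures rest on a constant hazard, on the planning risks of 12% and 8%, and on assumed visit timing, which the SAP does not give. They also assume that no bleed after the form reaches the outcome by another route, as the derivation now reads.

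With equal timing in both arms the risk ratio is almost unbiased. Bias in the ratio would need a timing difference by arm, which the SAP neither shows nor checks.

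**What to change.** 1. In 9.4 (Primary outcome measure), add bleeds reported on SAE forms as a source. Where the 12-month form is dated before day 365, confirm bleeding status to day 365 from the medical notes.
2. In 9.10, treat bleed-free participants whose last bleeding information precedes the end of the period as incompletely observed in the complete-case and multiple-imputation analyses. State whether that end is day 365 or the SAP's own day 351. Align the statement in 9.3 that no data are missing.
3. Tabulate the timing of the 12-month form by arm.
4. Reconcile the day-351 window (mortality and transplant-free survival) with ± 2 months (EQ-5D-5L paragraph and Appendix C).

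The visit window itself need not move. The cost is SAP wording, some extra notes checks, and slightly later closure of some forms.
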